## Abstract

**Background:**

Patients with acute decompensation of chronic heart failure often have residual fluid retention at hospital discharge, which is closely associated with high rates of rehospitalization and mortality during the post-discharge vulnerable phase. This “revolving door” phenomenon imposes a substantial economic burden on healthcare systems and contributes significantly to inpatient bed occupancy. Current clinical assessment methods are highly subjective and lack precise quantitative indicators. This study protocol proposes a randomized controlled trial aiming to use accurately quantifiable fluid overload measured by Bioelectrical Impedance Analysis-a non-invasive, cost-effective, and portable technology-to guide diuretic therapy and optimize volume management.

**Methods:**

This study is a single-center, open-label, randomized controlled trial with blinded endpoint assessment, and aims to enroll 538 participants at the First Affiliated Hospital of Xinjiang Medical University. Patients will be randomly assigned in a 1:1 ratio to either the intervention group (diuretic therapy guided by fluid overload measured using the Bioelectrical Impedance Analysis) or the control group (standard empirical treatment). The study aims to investigate the association between a volume management strategy guided by precise quantitative assessment of fluid overload and patient outcomes. The primary endpoint is the composite of heart failure rehospitalization or all-cause death within 3 months after discharge.

**Potential impact:**

The expected results of this study will demonstrate the clinical benefits of diuretic therapy guided by a precise volume management strategy, thereby improving treatment practices for hospitalized patients with heart failure and promoting the standardized application of this approach in heart failure management. At a broader level, this study provides a paradigm for exploring precision medicine in heart failure by integrating noninvasive monitoring technologies with conventional pharmacological therapy to improve key hard clinical endpoints. Ultimately, the study supports a shift in heart failure management toward a more individualized and goal-oriented approach, offering new insights and tools to reduce the burden of heart failure and improve long-term patient outcomes. The recruitment has started and is ongoing, and this protocol outlines the study's design, methodology, and implementation framework.

**Clinical Trial Registration:**

https://www.chictr.org.cn/, Chinese Clinical Trial Registry, ChiCTR2500111518.

## Introduction

Acute heart failure (AHF) is a clinical syndrome with rapid onset or sudden worsening of heart failure symptoms and signs, triggered by diverse etiologies. It is characterized by elevated plasma natriuretic peptides and often follows a life-threatening course that requires prompt medical intervention, frequently necessitating emergency hospitalization. Acute decompensation of chronic heart failure represents the predominant AHF phenotype, accounting for approximately 70%–80% of all AHF admissions, and is associated with poor prognosis. Registry data indicate that in-hospital mortality for AHF is approximately 12%, while the incidence of death or heart failure rehospitalization reaches 30%–45% within 90 days and 67% within one year (1). This high rate of readmissions places a substantial burden on global healthcare resources and leads to critical shortages in hospital bed capacity. Consequently, reducing potentially preventable readmissions has become a key priority for public health policy and hospital quality improvement programs worldwide.

This excess risk has been attributed to inadequate diuresis during index admission; over 50%–70% of patients are discharged with residual fluid overload (2–4). Conversely, intensified inpatient diuretic regimens attenuate congestion at discharge and improve post-discharge outcomes (3). Nevertheless, diuretic use and dose titration in AHF remain a double-edged sword. Early, aggressive diuresis rapidly relieves symptoms, shortens length of stay, and may reduce mortality (5). Conversely, the absence of precise guidance predisposes to over-diuresis, precipitating electrolyte disturbances, hypotension, and worsening renal function with resultant clinical deterioration (6, 7).

Determining the optimal approach to guide diuretic therapy, remove excess fluid, and improve clinical outcomes remains an unresolved challenge. Currently, traditional assessment methods, such as weight measurement, skinfold thickness, and calculation of Body Mass Index (BMI), have significant limitations in precisely determining the extent of fluid retention within the body. Established body-composition tools such as underwater weighing or dual-energy x-ray absorptiometry, although accurate, are invasive, require specialized equipment and trained personnel, and carry substantial cost, all of which preclude routine clinical use. Consequently, the pursuit of precise, quantitative, and non-invasive strategies for diuretic management continues to command intense international investigative interest.

Bioelectrical Impedance Analysis (BIA) can directly quantify fluid retention, providing a noninvasive method for precise assessment of fluid overload (8, 9). Evidence suggests that precision volume management strategies have already been integrated into the care of patients with renal dysfunction or those receiving dialysis; however, their application in the field of heart failure remains exploratory and is limited by a lack of evidence from large-scale randomized controlled trials (10, 11). Therefore, we designed a randomized controlled trial to address this gap and to evaluate the impact of diuretic therapy guided by precise fluid overload assessment on clinical outcomes in Chinese patients with acute decompensation of chronic heart failure.

## Methods and analysis

### Study objectives

The primary objective of this single-center, randomized controlled trial is to evaluate the impact of a precision fluid management strategy, guided by BIA, on clinical outcomes in patients hospitalized for acute decompensated heart failure, compared with standard empirical diuretic therapy.

The primary endpoint is the composite of heart failure rehospitalization or all-cause mortality within 3 months after discharge. The key secondary endpoints include the evaluation of individual components of the primary outcome, cardiovascular mortality, changes in quality of life as assessed by the Kansas City Cardiomyopathy Questionnaire (KCCQ) score, symptom relief measured by Visual Analogue Scale (VAS) score, and in-hospital diuretic utilization. The safety profile of the intervention, with specific regard to blood pressure, renal function, and electrolyte stability, will also be assessed.

### Study design

This investigator-initiated, single-center, two-arm, randomized controlled trial will be conducted at a tertiary hospital in Xinjiang, China to compare the incidence of composite endpoint events (heart failure rehospitalization and all-cause mortality) between the two groups over a 3-month follow-up period, thereby providing practical evidence to support the clinical application of this technology in this patient population.

A total of 538 adult patients clinically diagnosed with acute decompensation of chronic heart failure and who meet the inclusion and exclusion criteria. The intervention will be conducted during the patients’ hospitalization, and clinical assessments will be performed at 2 weeks, 4 weeks, and 12 weeks after discharge. Figure 1 shows the patient flow through the study. This study is registered at Chinese Clinical Trial Registry (ChiCTR2500111518).

**Figure 1 F1:**
[figure not shown]
Study flow diagram of the trial. BCM, Body Composition Monitor; OH, overhydration.

### Study population and recruitment

Eligible patients who meet all inclusion criteria and no exclusion criteria will be enrolled from the Department of Cardiology, The First Affiliated Hospital of Xinjiang Medical University. Potential participants will be approached, informed, and invited by the clinical team; during this process, a physician coordinator will explain the protocol, provide the informed-consent form, and confirm eligibility on the basis of clinical status. The specific inclusion and exclusion criteria are detailed in Table 1.

**Table 1 T1:** Inclusion and exclusion criteria.

Criteria Type	Specific Content
*Inclusion criteria*	1. Aged 18 to 75 years;
	2. Hospitalization for acute decompensated heart failure or worsening heart failure symptoms;
	3. Established prior diagnosis of chronic heart failure;
	4. Clinical evidence of fluid overload (e.g., pulmonary rales, peripheral edema, jugular venous distension, ascites, pulmonary congestion, or radiographic pulmonary edema) requiring intravenous diuretic therapy as determined by the treating physician;
	5. Provision of written informed consent.
*Exclusion criteria*	1. Have other serious diseases that may endanger survival within 3 months, and have rehospitalization plans (including revascularization, device implantation, etc.) within 3 months after discharge;
	2. The history of two or more electrolyte disturbances in the past year;
	3. Severe renal insufficiency (serum creatinine >442 μmol/L or eGFR <30 mL/(min·1.73m^2^), nephrotic syndrome or receiving long-term regular dialysis;
	4. Severe hypothyroidism and decompensated cirrhosis;
	5. Lower extremity cellulitis, severe varicose veins, lymphedema, or deep vein thrombosis;
	6. Pregnant or bedridden patients unable to take weight measurement;
	7. Patients presenting with fever or diarrhea upon hospital admission.

### Sample size

The sample size was calculated to test the superiority of a BIA-guided precision fluid management strategy over standard empirical diuretic therapy. Based on previous data, the 3-month incidence of the composite outcome of heart failure rehospitalization or all-cause mortality in the control group was assumed to be 24.9% (1). We hypothesized a 20% relative risk reduction with the intervention, corresponding to an expected event rate of 19.9% in the intervention group.

With a significance level of 0.05, a power of 80%, and a 1:1 randomization ratio, a total of 242 participants per group were required. Allowing for a 10% attrition rate, the final target sample size was increased to 269 participants per group, yielding a total sample size of 538. Sample size calculations will be performed using PASS software.

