The primary endpoint will be tested at a two-sided alpha level of 0.05. All secondary endpoints will be analyzed as exploratory; no formal multiplicity adjustment will be applied. For secondary and safety outcomes, effect estimates with 95% confidence intervals will be reported and interpreted cautiously.

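### The stated 242 per group gives about 26% power for 24.9% versus 19.9%, not 80%; those assumptions need about 1,091 per group

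*Protocol article*

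**What the plan says.** The Sample size section of the protocol article gives every input to the calculation.

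- Hypothesis: "The sample size was calculated to test the superiority of a BIA-guided precision fluid management strategy over standard empirical diuretic therapy".
- Control rate: 24.9% at 3 months, with reference 1 as its source.
- Effect: "We hypothesized a 20% relative risk reduction with the intervention, corresponding to an expected event rate of 19.9% in the intervention group".
- Result: "With a significance level of 0.05, a power of 80%, and a 1:1 randomization ratio, a total of 242 participants per group were required".
- Attrition: 10%, which raises the target to 269 per group and 538 in total.

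The Sample size section does not say whether the test is one- or two-sided. The Statistical analysis section does: "The primary endpoint will be tested at a two-sided alpha level of 0.05". That section also names the primary comparison, a log-rank test on time to first event, with a Cox model for the effect estimate. No formal interim efficacy analysis is planned.

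The Introduction, also citing reference 1, reports for acute heart failure that "the incidence of death or heart failure rehospitalization reaches 30%–45% within 90 days".

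**The concern.** A 5-point difference between rates in the 20% to 25% range normally needs around a thousand patients per arm, so 242 is too small on sight. Because the section states both the inputs and the answer, it can be checked directly.

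If the claimed 80% is really about 26%, a true 20% relative reduction would be missed about three times in four. A non-significant result could then be taken as evidence against the strategy, because the protocol says the trial was adequately powered for that effect. Recruitment is under way according to the abstract, so a correction made now, before results are known, is more credible than one made afterwards.

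**Working it through.** **Inputs.** p1 = 0.249, p2 = 0.199, power 80% and 1:1 allocation come from Sample size; two-sided alpha 0.05 comes from Statistical analysis. The normal quantiles are 1.960 and 0.8416. The mean rate is (0.249 + 0.199)/2 = 0.224.

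**Attrition step.** 242/0.9 = 268.9, rounded up to 269; 2 × 269 = 538. This reproduces, so the fault lies in the 242.

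**Required size, two proportions (pooled variance under the null).**

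n = [1.960·√(2·p̄·(1−p̄)) + 0.8416·√(p1(1−p1) + p2(1−p2))]² / (p1−p2)²

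- √(2 × 0.224 × 0.776) = 0.5896
- √(0.249 × 0.751 + 0.199 × 0.801) = √0.3464 = 0.5886
- n = (1.1556 + 0.4953)² / 0.05² = 2.7257/0.0025 = 1,090.3, so **1,091 per group**
- 1,091/242 = 4.5

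**Power at the stated size.** Power = Φ[(√n × 0.05 − 1.1556)/0.5886]

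- n = 242: Φ[(0.7778 − 1.1556)/0.5886] = Φ(−0.642) = **26.0%**
- n = 269: Φ[(0.8201 − 1.1556)/0.5886] = Φ(−0.570) = **28.4%**

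**Log-rank version (the planned primary test).**

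- Under proportional hazards, HR = ln(0.801)/ln(0.751) = 0.775, so ln HR = −0.2550.
- Schoenfeld events: 4 × (1.960 + 0.8416)²/0.2550² = **483**.
- Expected events: 242 × (0.249 + 0.199) = 108, or 269 × 0.448 = 121.
- Power: Φ(√108.4 × 0.2550/2 − 1.960) = Φ(−0.632) = 26.4%. With 121 events it is 28.8%.

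**Could another reading give 242?**

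| Reading | Needed per group |
|---|---|
| Two-sided, unpooled variance | 1,088 |
| Two-sided, arcsine | 1,089 |
| Two-sided, continuity correction | 1,130 |
| Two-sided, p2 = 0.1992 unrounded | 1,100 |
| One-sided 0.05 | 859 |
| Log-rank, HR 0.775 (483 to 489 events) | 1,079 to 1,092 |
| 20% reduction from 30% | 859 |
| 20% reduction from 37.5% | 623 |
| 20% reduction from 45% | 466 |

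None comes near 242. Even at a 45% control rate, 242 per group gives only about 52% power. Reading 242 as a total for both arms widens the gap.

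**What the planned size can detect.** With a 24.9% control rate, 80% power needs an intervention rate of about 14.8% at 242 per group (10.1 points; 41% relative reduction) or about 15.2% at 269 per group (39%).

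**Expected precision.** The 95% half-width for the risk difference at 242 per group is 1.960 × √(0.3464/242) = 1.960 × 0.0378 = 7.4 percentage points. The hypothesised difference is 5.0.

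**The case against.** The arithmetic has no good answer. That this is an article condensing a fuller protocol does not help, since nothing is left out: inputs and result are both printed and they disagree. Naming PASS as the software does not validate the output. No interim analysis or other stated design feature would reduce the sample size by such a factor.

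Four points on the other side deserve weight.

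- **Choice of remedy.** The document does not show whether the sample size, the effect or another input was entered wrongly. Restating the detectable effect for a fixed 538 must not be presented as if a 40% reduction had been the hypothesis. This stands.
- **Control rate.** The 24.9% and the 30% to 45% may describe different populations within one source. This trial excludes patients over 75, those with severe renal insufficiency and those with other disease threatening 3-month survival, so a lower rate is plausible. The source is not available here. The gap therefore calls for an explanation and is not itself a proven error; the finding does not depend on it.
- **Attrition.** Censored patients still contribute to a time-to-event analysis, so 26% to 29% is a fairer range than 26% alone. The conclusion is unchanged.
- **Reporting.** The planned hazard ratio with its 95% confidence interval would reveal the imprecision. That limits misreading but leaves the stated power wrong.

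**Conclusion.** The error is established and must be fixed. Under the protocol's own assumptions (24.9% versus 19.9%, two-sided 0.05, 1:1), 80% power needs 1,091 evaluable patients per group. The planned trial has 26% to 29% power, depending on attrition and on whether it is computed for proportions or for the log-rank test.

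The log-rank figures assume proportional hazards and follow-up to 3 months. The event counts are derived from the stated rates, as the article gives no event target. The conclusion is not sensitive to sidedness, variance formula, continuity correction or a control rate anywhere between 24.9% and 45%.

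The planned size corresponds roughly to a 10-point absolute difference rather than the stated 5 points. How the discrepancy arose cannot be told from the document.

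**What to change.** Rerun the calculation and correct the Sample size section so that its figures agree. The least costly correction keeps 538 and keeps the 20% reduction as the stated hypothesis. Suggested text:

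> With 242 evaluable participants per group (538 randomised, 10% attrition), the trial has about 26% power at two-sided 0.05 to detect 24.9% versus 19.9%. It has 80% power for a relative reduction of about 40% (24.9% to about 15%). The expected 95% confidence interval for the risk difference is about ±7.4 percentage points, so a non-significant result will not by itself exclude a 20% relative reduction.

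Also state the sidedness in that section, and explain why 24.9% was chosen when the Introduction gives 30% to 45% at 90 days from the same reference.

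This costs wording in the protocol, and in the registry entry if the power is stated there, plus a much less favourable published power. It needs no extra patients.

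If the sponsor wants 80% power for the stated effect, the target becomes 1,091/0.9 = 1,213 per group, 2,426 in total. That is 1,888 more than planned and would go through the sample-size amendment route described under Protocol amendments.

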### Randomization and allocation concealment

Participants will be randomly allocated in a 1:1 ratio using a computer-generated randomization sequence with variable block sizes (e.g., 4, 6, or 8). The randomization list will be prepared by an independent statistician and concealed from investigators involved in enrollment and clinical management. Allocation concealment will be ensured via a centralized electronic randomization module within the electronic data capture (EDC) system. Randomization will be performed only after eligibility confirmation and informed consent; prior to randomization, investigators responsible for screening and enrollment will have no access to the allocation sequence or the upcoming assignment.

Given the single-center design and relatively large sample size, stratified randomization was not implemented. Baseline characteristics, including diuretic exposure, will be assessed for balance between groups. If clinically meaningful imbalance is observed, adjusted analyses will be performed.

### Blinding

This is an open-label trial with blinded endpoint adjudication. An independent Clinical Events Committee (CEC), whose members are blinded to treatment allocation, patient identity, and all fluid load data, will adjudicate all potential primary and secondary endpoint events according to pre-specified, standardized definitions.

### Interventions

#### Run-in phase

Instrumentation: Ensure that the Body Composition Monitor (BCM, Fresenius, Germany) used for the measurement and assessment of fluid overload is properly calibrated and maintained in optimal working condition.Staff training: All healthcare personnel participating in the study will receive standardized training to ensure a thorough understanding of the study objectives, methodology, and procedures, as well as the correct use of the measurement devices and the proper interpretation of their results.Patient screening and enrolment: All participants must meet the predefined inclusion and exclusion criteria, and written informed consent must be obtained prior to enrollment. Participants will be informed of the measurement procedures and any lifestyle modifications or treatment regimens required during the intervention period. Randomization will be completed within 24 h of hospital admission.

#### Intervention strategy

During hospitalization, BCM measurements will be conducted at a fixed time daily to quantify overhydration (OH) and guide daily diuretic adjustments.

Patients with OH > +1.1 L will be considered overhydrated and receive protocol-guided intensification of diuretic therapy, including an increase in the intravenous dose of loop diuretics by 25%–50% compared to the previous day. Both intermittent intravenous bolus and continuous intravenous infusion of loop diuretics are permitted during the trial, at the discretion of the treating physician. The mode of administration will be prospectively recorded and considered in exploratory subgroup and sensitivity analyses. If diuretic response remains inadequate, further escalation or the addition of predefined synergistic diuretics will be permitted. Patients with OH within the normal range (−1.1 L to +1.1 L) will receive maintenance or de-escalated diuretic therapy, with encouragement to transition to oral maintenance dosing when clinically stable (12). For patients with OH < −1.1 L, diuretic doses will be reduced by ≥50% or temporarily withheld for 24 h, and volume status will be reassessed to avoid hypovolemia.

Insufficient diuretic response is defined as failure to achieve at least one of the following within 24–48 h after dose adjustment: 1) net negative fluid balance of at least 500 mL per day, 2) body weight reduction of at least 0.5 kg, or 3) improvement in congestion-related symptoms. Clinical stability defined as relief of congestion symptoms, stable hemodynamics, and no requirement for intravenous diuretics for at least 24 h.

In cases of insufficient response, further escalation of loop diuretic dose or the addition of a synergistic diuretic agent (e.g., thiazide-type diuretics or mineralocorticoid receptor antagonists) will be permitted within guideline-recommended dose ranges, at the discretion of the treating physician.

BCM measurements will be performed using the Body Composition Monitor (Fresenius Medical Care, Germany) with standard wrist-to-ankle electrode placement according to the manufacturer's instructions. Measurements will be conducted once daily in the morning before intravenous diuretic administration. Participants will rest in a supine position for at least 5–10 min prior to measurement and will be instructed to refrain from excessive fluid intake for at least 2 h before the assessment.Overhydration (OH) values will be automatically calculated using the device's validated algorithm. Detailed measurement procedures are provided in Supplementary File S1. If a BCM measurement is not feasible on a given day, the reason must be documented, and volume management for that day will revert to protocol-defined clinical assessment criteria.

Safety triggers for de-escalation or interruption of diuretic therapy will include hypotension, worsening renal function, or clinically significant electrolyte abnormalities. In such cases, treating physicians will be allowed to deviate from the algorithm to ensure patient safety. All recommended adjustments and actual treatments will be prospectively documented, and protocol deviations will be recorded for subsequent per-protocol and sensitivity analyses.

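### Mode of diuretic administration, chosen after randomisation, is planned as a subgroup and sensitivity factor; within-mode comparisons can be biased either way, and the per-protocol use of deviations needs a similar guard

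*Protocol article*

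**What the plan says.** Protocol article, Interventions. The run-in paragraph has randomisation completed within 24 h of admission. Intervention strategy then allows bolus or continuous infusion of loop diuretic, with the choice left to the treating physician over the course of the trial, and continues: "The mode of administration will be prospectively recorded and considered in exploratory subgroup and sensitivity analyses".

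Later in the same section, hypotension, worsening renal function and electrolyte abnormality are listed as safety triggers. When one occurs, "treating physicians will be allowed to deviate from the algorithm to ensure patient safety". Recommended and actual treatment are both documented, and "protocol deviations will be recorded for subsequent per-protocol and sensitivity analyses".

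Control strategy states that BCM is not used in the control group, where titration rests on clinical judgement. Blinding describes an open-label trial with blinded adjudication.

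Statistical analysis places all analyses under intention to treat and names no per-protocol analysis. It also states: "The primary endpoint will be tested at a two-sided alpha level of 0.05". Under Missing data handling, subgroup analyses are called exploratory, with age and ejection fraction given as examples alongside other clinically relevant factors.

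**The concern.** A subgroup comparison keeps the protection of randomisation only if the subgroup is fixed before allocation. Mode of administration is not fixed in that way here. A physician who knows the arm decides it while treatment is under way, and may well decide it by how ill the patient is. If the arms also use infusion at different rates, the infusion patients of one arm differ in prognosis from those of the other, and so do the bolus patients. The treatment contrast within each mode then mixes any effect of the strategy with case mix. With one threshold of severity per arm, both strata lean the same way, so agreement between them could be misread as confirmation.

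The per-protocol analysis carries a related risk. Departures from the BCM algorithm can occur only in the arm that has one, and the triggers that permit them are prognostic events and mirror the trial's safety endpoints. If such departures led to exclusion, higher-risk patients would leave one arm only.

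At stake is the reading of supporting analyses in an open-label trial, not the primary result.

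**Working it through.** **Inputs from the document.** The control risk at 3 months "in the control group was assumed to be 24.9"%. The planned effect is a 20% relative reduction, "corresponding to an expected event rate of 19.9% in the intervention group"; check: 0.249 × 0.80 = 0.199, which reproduces. This 20% is a yardstick for the size of bias.

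**Assumed inputs, not in the document.** Strength of the severity effect, share of infusion in each arm, how closely mode follows severity, share of patients leaving the algorithm, and their risk. Ranges are shown for the shares, the mode-severity correlation and the risk of those leaving.

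**Part 1: comparison within mode, no true effect.** Severity U is standard normal in both arms. Risk is 1 − exp(−λ·exp(0.7U)), with λ = 0.244 so that mean risk is 24.9%. Infusion goes to patients whose latent mode score, correlated ρ with U, lies above the arm's cut-point. RR is BIA over control.

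| Infusion, control v BIA | ρ | Bolus risk, control v BIA | RR bolus | Infusion risk, control v BIA | RR infusion |
|---|---|---|---|---|---|
| 30% v 50% | 1 | 17.2% v 13.9% | 0.81 | 42.9% v 35.9% | 0.84 |
| 30% v 50% | 0.5 | 21.2% v 19.3% | 0.91 | 33.4% v 30.5% | 0.91 |
| 30% v 50% | 0.3 | 22.8% v 21.6% | 0.95 | 29.9% v 28.2% | 0.94 |
| 30% v 40% | 1 | 17.2% v 15.5% | 0.90 | 42.9% v 39.1% | 0.91 |
| 30% v 30%, same rule | any | equal | 1.00 | equal | 1.00 |
| 50% v 30% | 0.3 | 21.6% v 22.8% | 1.06 | 28.2% v 29.9% | 1.06 |
| 50% v 30% | 0.5 | 19.3% v 21.2% | 1.10 | 30.5% v 33.4% | 1.10 |
| 50% v 30% | 1 | 13.9% v 17.2% | 1.24 | 35.9% v 42.9% | 1.20 |

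The sign follows which arm uses more infusion. The size follows how closely mode tracks severity.

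A second model gives the same picture. It has 30% severe patients, with relative risk 1.5 to 3 for severe against other patients. If infusion is kept mainly for severe patients in control (10% of the less severe, 60% of the severe) and used more freely in the BIA arm (40% to 60% and 70% to 80%), the infusion-stratum RR is 0.89 to 0.71. With the freer use in control instead (40% and 70%, against 10% and 60% in BIA), it is 1.12 to 1.31. In this model the bolus stratum barely moves (0.98 to 1.03).

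**Part 2: per-protocol set, no true effect, exclusions in the BIA arm only.** With share s excluded at risk r, the remaining risk is q = (0.249 − s·r)/(1 − s), and HR = ln(1 − q)/ln(0.751).

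Example: s = 0.20, r = 0.40 gives q = (0.249 − 0.080)/0.80 = 0.211, and HR = ln(0.789)/ln(0.751) = 0.83.

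| Risk of those excluded | s = 10% | s = 15% | s = 20% |
|---|---|---|---|
| 24.9% | 1.00 | 1.00 | 1.00 |
| 30% | 0.97 | 0.96 | 0.94 |
| 40% | 0.92 | 0.88 | 0.83 |
| 50% | 0.87 | 0.80 | 0.72 |

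**Part 3: simulation check.** 4,000 null trials per setting with 242 per arm, latent severity driving outcome, departure and mode, and infusion used more freely in the BIA arm. A nominally significant false benefit occurred in 2.4% to 2.5% of intention-to-treat comparisons (nominal 2.5%), 6.0% to 9.8% of per-protocol comparisons and 5.6% to 11.2% of within-mode comparisons. These settings lean towards BIA by construction; they show that false positives can occur, not how often they would here.

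**The case against.** Much of the case on the other side stands.

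First, a reader might infer that mode is a consequence of the BIA algorithm and that the bias must therefore favour BIA. The document does not support that. Intensification is described as a dose increase; nothing ties bolus or infusion to the overhydration value or to the arm. Direction is open, and a false benefit as large as the planned 20% reduction needs perfect sorting by severity together with clearly more infusion in the BIA arm.

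Second, a reader might infer that the sickest BIA patients will be removed from the per-protocol set and no control patients will be. That too goes beyond the text. The article says that deviations are recorded for per-protocol use but gives no exclusion rule, and does not say whether a departure that the protocol permits counts as a deviation. A fuller protocol or analysis plan may settle this. Control patients can also deviate, for example on eligibility, the 24 h randomisation limit, visit windows or the bar on BCM. Only departures from the algorithm are one-sided.

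Third, all patients need intravenous diuretic at entry and randomisation may follow admission by up to 24 h, so some will already have a mode before allocation. The article does not say which mode would be used, although its wording points to mode during the trial.

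Fourth, the mode analyses are labelled exploratory. That limits the weight they carry, but the label does not remove selection bias. Nor is the choice of factor merely left to another document: the article itself names mode.

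**Conclusion.** The point on mode holds as a stated analysis rule that conditions, in general, on a post-randomisation choice by an unblinded physician. Under no true effect the within-mode risk ratio ranges from about 0.81 to 1.24 when infusion use is 30% in one arm and 50% in the other and the mode-severity correlation is 0.3 to 1. The second model, with its own assumptions, reaches 0.71 to 1.31 in the infusion stratum. Bias is nil if mode is chosen identically in both arms. No figure for mode use by arm or severity is in the document, so neither size nor direction can be predicted.

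The per-protocol point is conditional. If permitted safety departures were counted as exclusions, the hazard ratio under no effect would be about 0.97 to 0.72 for 10% to 20% excluded at an assumed 30% to 50% risk, and 1.00 if those patients had average risk. Separately, the mention of per-protocol analyses and the statement that all analyses follow intention to treat must be reconciled.

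The primary comparison by randomised arm is not affected. This should be corrected, but it does not threaten the main result.

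**What to change.** All changes concern the analysis; none touches a treatment rule.

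1. Report mode of administration descriptively by arm and drop it as a subgroup or sensitivity factor. Alternatively, keep it but define it as the mode already in place before randomisation.
2. Limit subgroup factors to values fixed before randomisation.
3. State that safety-triggered departures which the protocol permits count as adherent when the per-protocol set is formed.
4. Define per-protocol exclusions by criteria that can occur in both arms, such as ineligibility, assigned strategy never started, or crossover.
5. Amend the intention-to-treat sentence in Statistical analysis so that it governs the primary analysis and names the per-protocol analysis as supportive, or remove the per-protocol reference from Intervention strategy.

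The cost is a few sentences and at most one exploratory table. No data collection or sample size changes.
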